### Baseline

At baseline, patients will be asked to fill quality of life questionnaires (EQ-5D, AVVQ and CIVIQ; Additional files 1, 2 and 3) and will have their clinical scores assessed (CEAP and VCSS; Additional files 4 and 5). On discharge after their varicose vein intervention, the patients will then be provided with a diary to record their post-procedural pain every day for 10 days using a validated visual analogue scale (VAS) as well as to record when they return to their normal activities and are back to work (Additional files 6 and 7, respectively). They will also be asked to attend a follow-up in 2 weeks and at 6 months.

### ClariVein® technique

Patients will be consented for ClariVein®, being a relatively new technique under study. All patients will receive a procedure-specific information leaflet in their native language, which explains the technique including risks and side effects as well as a description of alternative techniques. Patients who do not want to be treated with ClariVein® will be routinely offered treatment with RFA (radiofrequency ablation), VenaSeal™ or open surgery.

In keeping with local preference, patients will be offered the procedure under local anaesthetic (lidocaine 1%) ± sedation. Antibiotics at induction will be routinely given. The patient is positioned supine with a sandbag under the knee to enhance access to the GSV. The SSV can be treated with the patient placed either prone or in the lateral position depending on the surgeon’s preference. A Seldinger technique is used to introduce a micro-catheter 4-F or 5-F introducer sheath into either the great saphenous vein (GSV) or the short saphenous vein (SSV) under ultrasound guidance and flushed with saline. The ClariVein® infusion catheter tip is inserted through the sheath and the tip of the dispersion wire is positioned 20 mm distal to the SFJ, or for the SSV just proximal to the fascial curve. Wire rotation is activated for a 3-s period to induce spasm of the proximal vein prior to commencing pullback. With the wire continuing to rotate, infusion of the sclerosant is started simultaneously with catheter pullback. The activated catheter, which is connected to a 9-V battery-motorised handle, is steadily withdrawn at 1 cm every 7–8 s. The sclerosant used will be 2.0% liquid sodium tetradecyl sulphate (STS) for both the GSV and the SSV. The sclerosant volume used will be 0.1–0.2 ml every 1-cm pullback and will be determined by the vein diameter and overall treatment length. A completion Duplex ultrasound will be performed after the procedure to confirm the patency of the common femoral vein and the deep venous system, and to ascertain whether there is any flow within the truncal vein and whether it is still compressible. The ipsilateral foot will be dorsi-flexed and plantar-flexed in order to minimise deep venous stasis at the end of the procedure [15]. Subcutaneous heparin is routinely given after the procedure to minimise the risk of deep vein thrombosis. A full-length compression bandage (Class II; Coban lite™) will be applied to the treated limb(s) from the foot to the groin. The patient will then be advised to undertake light exercise (3 × 15-min walks on the same day) when they felt well enough to do so. Bandages will be removed in 24 h and patients will be advised to wear compression stockings for 1 week during the daytime if the patient is randomised to the compression arm of the study. Otherwise, the patient will be discharged without compression hosiery.

### Follow-up

Patients will be followed up in the outpatient clinic at 2 weeks and 6 months. At the 2 weeks’ follow-up, the diary containing details of the pain scores and how soon patients were able to return to normal activities/work will be collected. In addition, patients will be asked about any bruising or phlebitis they have had in the 2 weeks after their procedure and how compliant they have been with the compression. The degree of bruising and phlebitis will be assessed using a pre-determined score (0, 0%; 1, < 25% of treated vein affected; 2, 25–50% of treated vein affected; 3, 50–75% of treated vein affected; 4, 75–100% of treated vein affected; and 5, extending beyond the treated vein). They will be examined and the Venous Clinical Severity Score (VCSS) will be recorded. They will also be asked to fill in the EQ-5D, AVVQ and CIVIQ scores. They will have a venous Duplex scan to determine occlusion of the treated vein. Recanalisation will be defined by a segment ≥ 5 cm.

At the 6-month follow-up, patients will be examined and their VCSS will be recorded. They will also be asked to fill in the EQ-5D, AVVQ and the CIVIQ scores. They will have a venous Duplex scan to determine occlusion of the treated vein. An overall satisfaction survey will also be asked. A flowchart for the trial is provided in Fig. 1. The study timeline is also detailed in the SPIRIT (Standard Protocol Items: Recommendations for Interval Trials) schedule of enrolment, interventions and assessments in Fig. 2. The SPIRIT checklist is included in Additional file 8.

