## Methods

### Aims

The primary aim of the study is to assess patient’s pain scores for the first 10 days post procedure using a visual analogue scale (VAS). Secondary aims are to compare the two treatment groups with respect to: quality of life scores at baseline, 2 weeks and 6 months using the EQ-5D (EuroQol 5 Dimensions), AVVQ (Aberdeen Varicose Vein Questionnaire) and CIVIQ (ChronIc Venous Insufficiency quality of life Questionnaire) scores; clinical change using the VCSS (Venous Clinical Severity Score) at baseline, 2 weeks and 6 months; the degree of bruising (mild, moderate and severe) and phlebitis at 2 weeks and 6 months; patient compliance with the intervention; time taken to return to work and normal activities; patient satisfaction, assessed with a patient satisfaction questionnaire; and successful obliteration of the target vein, assessed with duplex ultrasound scan at 6 weeks and 6 months. Recanalisation will be defined by a segment of vein ≥ 5 cm. A comparison of the cost-effectiveness of the intervention will also be carried out.

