### Statistical analysis

All analysis will be undertaken on an intention-to-treat basis. Pain score data will be treated as non-parametric and compared using the Mann–Whitney *U* test. Multivariable predictors for higher VAS pain scores will be determined using linear/non-linear regression. Other continuous data will be compared by the Student *t* test or Mann–Whitney *U* test for parametric and non-parametric data, as appropriate. The median and first and third quartiles will be reported for continuous variables. Categorical data will be compared by the chi-square test or Fisher’s exact test, as appropriate, with a *P* value less than 0.05 indicating significance. The 5% level will be considered significant throughout. The individual undertaking the analyses will be blinded to trial allocation.

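### Return-to-work and return-to-activity times are cut off when the diary is collected at 2 weeks, but the stated tests make no provision for patients not yet back

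*Protocol article*

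**What the plan says.** The Aims section of the protocol article lists "time taken to return to work and normal activities" among the secondary comparisons. Under Baseline, patients receive a diary at discharge for ten days of pain scores "as well as to record when they return to their normal activities and are back to work". The ten-day limit belongs to the pain scores; no last day is given for the return dates.

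Under Follow-up, at 2 weeks the diary with the pain entries and "how soon patients were able to return to normal activities/work will be collected". The 6-month visit is then itemised: clinical severity score, quality-of-life questionnaires ("They will also be asked to fill in the EQ-5D, AVVQ and the CIVIQ scores"), duplex scan and satisfaction survey. No question about return to work or activities appears there.

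The Statistical analysis section gives pain its own test and then states "Other continuous data will be compared by the Student *t* test or Mann–Whitney *U* test", the choice depending on whether the data are parametric. Categorical data go to chi-square or Fisher's exact test. No time-to-event method is named and the return times are not mentioned individually. The section also says "All analysis will be undertaken on an intention-to-treat basis".

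**The concern.** A duration in days fits only the rule for other continuous data. Anyone not back when the diary is handed in has no duration to enter, only the knowledge that it exceeds about 14 days. That gap is caused by the outcome itself, because only slow recoverers can have it.

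If the tests are run on whatever numbers are in the diaries, the slower arm loses more of its patients, and those it loses are its worst. What remains makes the arms look more alike than they are. At stake is a diluted comparison of a patient-relevant secondary outcome, with a real benefit of either policy more easily missed. The primary pain comparison is not affected.

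**Working it through.** The article gives no return times, no spread and no share of patients not back at 2 weeks. There is therefore no figure of its own to reproduce, and everything numerical below is illustration.

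**Inputs from the article:** 47 patients per group (Sample size and study duration); cut-off at day 14 (2-week diary collection, Follow-up); 5% level (Statistical analysis), taken as two-sided because the article does not say.

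**Assumptions:** exponential return times rounded up to whole days; a share pA (compression) and pB (no compression) not back by day 14. Which arm is slower is arbitrary.

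**Formulas.**
- Mean return time: m = 14 / (−ln p).
- Mean among those back by day 14: m − 14p/(1 − p).
- Expected number without a value: 47 × (pA + pB).

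**Worked case, 5% and 15%.**
- All patients: 14/2.996 = 4.67 days and 14/1.897 = 7.38 days, a difference of 2.71 days.
- Recorded values only: 4.67 − 14 × 0.05/0.95 = 3.94 and 7.38 − 14 × 0.15/0.85 = 4.91, a difference of 0.97 days.
- Without a value: 47 × 0.20 = 9.4 of 94.

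The simulated differences, with whole-day rounding, are 2.68 and 0.95 days, which agrees.

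**Power.** Simulation with 3,000 trials per row. The Monte Carlo standard error is at most √(0.25/3000) = 0.9 percentage points. The three power columns are Mann-Whitney with complete follow-up, with patients lacking a value excluded, and with those patients kept at a tied top rank.

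| Not back, A / B | Without a value, of 94 | Mean difference, all / recorded only (days) | Complete | Excluded | Kept, ranked last |
|---|---|---|---|---|---|
| 0.1% / 1% | 0.5 | 0.99 / 0.87 | 38% | 36% | 38% |
| 1% / 5% | 2.8 | 1.61 / 1.02 | 42% | 32% | 42% |
| 2% / 10% | 5.6 | 2.49 / 1.23 | 58% | 37% | 58% |
| 5% / 15% | 9.4 | 2.68 / 0.95 | 48% | 22% | 47% |
| 10% / 25% | 16.5 | 4.07 / 0.92 | 57% | 18% | 55% |

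Rows should be read across, not down, because the true effect differs between them. A t test on recorded values does no better at the larger shares: 24% power at 5%/15% and 18% at 10%/25%.

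**No true difference (10% / 10%).** With exclusion, the rejection rate is 4.7% for Mann-Whitney and 4.8% for the t test. The harm is dilution, not false positives.

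**Sensitivity to shape.** A second simulation (1,500 trials per scenario, 47 per arm) compared log-rank on all patients with Mann-Whitney after exclusion, so the test differs as well as the handling.
- Exponential medians of 4 and 6 days (8.7% and 19.6% not back): 44% against 16%.
- Lognormal medians of 3 and 5 days, sigma 0.8 (2.7% and 9.8% not back): 79% against 72%.

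The direction is the same, but the size depends strongly on the shape as well as on the share not back.

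**The case against.** The strongest reply is that nothing in the article excludes anyone. A reader might infer that the slowest patients drop out by design and that the intention-to-treat commitment is therefore broken. The text supports neither inference: no exclusion is written, the commitment points the other way, and it would fail only if an analyst chose to discard these patients.

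Mann-Whitney can also keep them at the highest rank at almost no cost (47% against 48% in the 5%/15% row). The article reports medians and quartiles. With these patients kept, the median stands as long as fewer than half are censored, and the third quartile as long as fewer than a quarter are. The coding rule might sit in the full protocol, the SAP or the diary form, none of which is shown. The schedule figure is also missing, so a later question cannot be wholly ruled out. Finally, the share not back may be small: treatment is under local anaesthetic with or without sedation, walking is advised the same day, and patients needing concurrent phlebectomies are excluded.

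Most of this stands, and it limits the size of the point. It does not remove it, because the article itself fixes a cut-off and a family of tests that do not fit together. The t test is one of the permitted choices and needs a number for every patient; any number put in for those not back would be a convention that the plan does not state. An SAP can add a ranking rule, but it cannot recover dates after day 14 that no visit asks for.

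**Conclusion.** The point holds in a limited form. Both return times are right-censored at about day 14, and the stated tests make no provision for patients not yet back. If recorded values alone are tested, the group difference shrinks and power falls, while type I error stays near 5% with equal arms.

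The size cannot be fixed from the document. Under exponential times it runs from negligible (38% to 36% when about 1% or fewer are not back) to more than half the power lost (48% to 22% at 5% and 15%). It would be wrong to quote any one of these as the expected loss, since all rest on assumed return times. This is a secondary-outcome matter that should be settled before recruitment, not a threat to the trial's main conclusion.

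**What to change.** State in the Statistical analysis section that return to work and return to normal activities are each analysed as time-to-event from the procedure date. Use Kaplan-Meier curves and a log-rank test, and censor patients not yet back at the date their diary is collected. This uses each patient's own collection date, so some variation around 2 weeks does no harm.

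If the simpler test is preferred, the minimum is Mann-Whitney with patients not yet back kept and ranked last at a common day-14 cut-off, and no t test for these two outcomes.

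Optionally, ask patients not back at 2 weeks for their return date at the existing 6-month visit. The downside is one recalled item.

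The cost is one sentence in the analysis section and, if wanted, one question at a visit already planned. The Trial status section says recruitment has not begun, so both can be in place before any data exist. If nobody turns out to be censored, almost nothing is lost.

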**Fig. 1 Fig1:**
[figure not shown]
COMpression Therapy Following MechanO-Chemical Ablation (COMMOCA) randomised controlled trial flow chart. AVVQ Aberdeen Varicose Vein Questionnaire, CIVIQ ChronIc Venous Insufficiency quality of life Questionnaire, EQ-5D EuroQol 5 Dimensions, MOCA mechano-chemical ablation, VCSS Venous Clinical Severity Score

**Fig. 2 Fig2:**
[figure not shown]
Standard Protocol Items: Recommendations for Interventional Trials (SPIRIT) flow sheet schedule of enrolment, interventions and assessments. AVVQ Aberdeen Varicose Vein Questionnaire, CIVIQ ChronIc Venous Insufficiency quality of life Questionnaire, EQ-5D EuroQol 5 Dimensions, MOCA mechano-chemical ablation, VCSS Venous Clinical Severity Score

### Sample size and study duration

The sample size needed to observe a difference of at least 20 mm in the VAS score with a standard deviation of 20 mm was estimated. With power of 90% and 5% significance equivalence, a minimum of 94 patients (47 per group) will need to be recruited. Accounting for losses to follow-up in the order of 10% gives a target sample size of 103 patients.

Previous studies looking at compression stockings have shown high drop-out rates close to 40% at 3 months. We do not anticipate this problem with the set up in the outpatient clinic at Changi General Hospital in Singapore. If we estimate 10% drop-out, this would mean we would need near to 200 patients to be included in this study. If three patients are recruited per week, this would take approximately 17 months to recruit the necessary number of patients. With 6 months follow-up, therefore, the study will be running for 23 months, but 3 years would give a good safety net for recruitment and follow-up, and allow for dropouts. We aim to have recruited 100 patients within the first 12 months of the study.

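### The printed sample-size inputs (20 mm, SD 20 mm, 90% power, 5%) need about 23 to 24 per group, not 47, so at least one printed figure is misstated and the article does not show which

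*Protocol article*

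**What the plan says.** Under Sample size and study duration, the protocol article gives its basis as "a difference of at least 20 mm in the VAS score with a standard deviation of 20 mm was estimated". It continues: "With power of 90% and 5% significance equivalence, a minimum of 94 patients (47 per group) will need to be recruited". A 10% allowance for loss then brings the target to 103. The next paragraph, using the same 10%, arrives at a figure near 200.

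Under Statistical analysis, the test for the primary outcome is fixed: "Pain score data will be treated as non-parametric and compared using the" Mann–Whitney *U* test. The same section adds: "The 5% level will be considered significant throughout". Neither section gives an equivalence margin, a pair of one-sided tests or a confidence-interval rule. No design effect or multiplicity adjustment is mentioned that could account for a larger number.

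**The concern.** A difference equal to one standard deviation is a large effect and normally needs a little over 20 patients per group for 90% power. The stated 47 is about twice that. This is the only sample-size justification in the article, and a reader cannot recover from it what the trial is designed to detect.

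The possible explanations differ in consequence. If 20 mm and SD 20 mm are the true inputs, the trial has a large reserve for its primary comparison. If the SD actually used was near 30 mm, there is no reserve and 47 per group falls just short of 90%. That matters because the article itself recalls drop-out close to 40% in earlier stocking trials. Its Discussion also foresees recalculating the sample size if drop-out exceeds expectation (there with recanalisation in view). A recalculation needs a starting figure that can be reproduced.

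The word equivalence adds a second uncertainty, since it names a hypothesis that neither the sizing sentence nor the analysis section pursues.

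**Working it through.** **Inputs, all from Sample size and study duration unless noted**
- Difference δ = 20 mm and SD σ = 20 mm, so δ/σ = 1.0.
- Power 90%, z = 1.2816.
- Significance 5%. Sidedness is not stated; two-sided is assumed (z = 1.960) and one-sided is also tried.
- Two equal groups: "a minimum of 94 patients (47 per group) will need to be recruited".
- Test: Mann–Whitney (Statistical analysis).

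**Attempt to reproduce 47 per group**

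Normal approximation: n = 2(1.960 + 1.2816)² × (20/20)² = 21.01, so 22 per group. The exact t-test needs 22.02, so 23 per group and 46 in total.

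For Mann–Whitney under normality (relative efficiency 3/π ≈ 0.955), 22.02/0.955 = 23.06, so 24. Simulation agrees: power is 0.893 at 23 per group and 0.909 at 24. With the worst-case efficiency of 0.864, 22.02/0.864 = 25.49, so 26.

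Other readings of the same sentence:

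| Reading | Per group |
|---|---|
| One-sided 5%, difference | 18 |
| Equivalence, margin 20 mm, true difference 0, one-sided 5% tests: 2(1.645 + 1.645)² = 21.6 | 22 |
| Equivalence, same margin, one-sided 2.5% tests | 26 |
| Non-inferiority, margin 20 mm | 18 to 22 |
| SD multiplied by √2: 2 × 21.01 = 42.03 | 43 |
| Bonferroni over ten diary days (0.5%), exact t | 36 |

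None gives 47.

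**Power at 47 per group for 20 mm and SD 20 mm**
- t-test: 99.8%.
- Mann–Whitney, simulated: 99.7%.
- Mann–Whitney, worst-case efficiency: 99.4%.

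**What would fit 47 per group at 90% power (t-test)**
- SD 20 mm: a difference of 13.5 mm. For Mann–Whitney, 13.5/√0.955 ≈ 13.8 mm.
- Difference 20 mm: an SD of about 29.6 mm.
- With SD 30 mm the normal approximation is 21.01 × (30/20)² ≈ 47.3, close to the printed figure. The exact t-test needs 48.26, so 49, and 47 per group gives 89%.

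**Recruitment figures**
- Allowing for 10% loss: 94/(1 − 0.10) = 104.4, so 105.
- The printed 103 matches 94 × 1.1 = 103.4.
- Recruiting 103 and losing 10% leaves 103 × 0.9 = 92.7 evaluable, just under 94.
- The figure near 200 cannot be reached from 94 with 10% drop-out.

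**The case against.** The strongest reply is that the discrepancy runs in the safe direction. Taken at face value, 94 patients more than cover a 20 mm difference, so the primary comparison is not put at risk and the correction is one of reporting. This stands, provided the printed SD is the one used. It does not make the sentence right: the article calls 94 a minimum for 90% power, and the only inflation it mentions is added after that figure.

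A second reply is that the power may be about right and only the SD misprinted, since an SD of 30 mm nearly reproduces 47. That also stands as a possibility, so it would go too far to say that the 90% figure is definitely the error. For the same reason, a reader might infer that the total of 46 was mistaken for a per-group number, or that twice the necessary patients are being recruited. The article supports neither inference, because it does not show how 47 arose.

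A reader might also infer from the word equivalence that a non-significant result is meant to count as equivalence. The documents do not support that. The text speaks of observing a difference, the analysis is a test of difference and no margin exists. A wording slip for significance level is the likeliest explanation.

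Finally, one might try to settle the true inputs from the laser-ablation trial in the Background (mean VAS 3.7 versus 2.0 at 1 week). It compared two durations of stocking wear after a different procedure. Its difference is 17 mm only if the scale is assumed to run from 0 to 10, and its SDs (2.1 and 1.1) are not the 20 mm used here. It is no benchmark for this calculation.

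**Conclusion.** The printed difference, SD, power and sample size are mutually inconsistent. The stated inputs need 23 per group by t-test and 24 by the planned test (26 at worst), against 47 stated. At 47 per group, power for 20 mm is about 99.8%, against 90% stated. One or more of the four figures is wrong, and the article does not identify which.

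This rests on a two-sided 5% level and equal groups; a one-sided level widens the gap. The Mann–Whitney figures of 24 per group and 99.7% assume normally distributed scores.

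The 20 mm target is not underpowered if SD 20 mm is right. If the SD was 30 mm, power is about 89% by t-test, slightly below the claim. The equivalence wording is a minor error of expression. The recruitment totals of 103 and near 200 contradict each other under the same 10% drop-out, and neither equals 94/0.9.

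**What to change.** State the inputs actually used and restate the result from them:

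- If 20 mm and SD 20 mm are correct, keep the planned size and report that 47 per group gives about 99.8% power for 20 mm (99.7% by Mann–Whitney). The smallest difference detectable with 90% power, about 13.5 mm by t-test, can be added as information. It should not be written in as a new target, because it is solved backwards from 47 and has no rationale in the protocol.
- If SD 30 mm was used, print it and report 89% power at 47 per group.

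Replace the word equivalence with level, so that the sentence reads as a two-sided 5% significance level.

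Reconcile the recruitment figures: 94 evaluable with 10% loss needs 105 recruited, and the figure near 200 should be explained or removed.

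The cost is protocol wording, plus about two patients (105 rather than 103) if 94 evaluable are to be kept. Under Trial status, recruitment had not begun, so the correction can be made before any data exist.

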### Study setting

The trial will take place in Singapore General Hospital, Singapore and Roscommon University Hospital, Ireland.

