## Discussion

The role of compression following endovenous interventions for superficial venous reflux remains unclear. If indicated, the optimal duration of treatment is also obscure. Non-tumescent, non-thermal (NTNT) endovenous techniques are increasingly used as they facilitate a more office-based approach to venous interventions. The COMMOCA trial will provide valuable data regarding the role of compression as an adjunct to one of the NTNT techniques. The primary aim of the study is to assess patient’s pain scores for the first 10 days post procedure using a visual analogue scale. Secondary aims include an assessment of patient compliance with compression, quality of life scores, clinical effectiveness, rates of bruising and phlebitis, time taken to return to normal activities, patient satisfaction and occlusion rate at 6 months.

This trial has some potential weaknesses, including the simple randomisation technique which has been chosen. This may lead to issues such as the production of unequal sample sizes. Additionally, the potential for losses to follow-up is a weakness in any trial of venous interventions. Short-term outcomes such as pain score are relatively straightforward to capture. However, early recurrence and recanalisation rates are of major concern to interventionists and require longer follow-up. COMMOCA is set in two established ambulatory venous centres with pathways for follow-up already in place. Between them, the two centres undertake over 1000 superficial venous procedures per annum. Six-month follow-up completion rates will be monitored closely throughout the trial. If necessary, the sample size will be recalculated to reflect a greater than expected drop-out rate and ensure sufficient statistical power regarding recanalisation rates at the end of the trial.

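### The protocol gives two irreconcilable recruitment targets, 103 and about 200, for the same 10% drop-out, and the base of 94 does not follow from its stated inputs

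*Protocol article*

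**What the plan says.** All figures are in the protocol article, Methods, *Sample size and study duration*, unless another section is named.

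- **First paragraph.** The trial is sized on a VAS pain difference of 20 mm with an SD of 20 mm. The error rates are given as "With power of 90% and 5% significance equivalence", leading to at least 94 patients, 47 per group. Then: "Accounting for losses to follow-up in the order of 10% gives a target sample size of 103 patients".
- **Second paragraph, target.** After noting drop-out close to 40% in earlier stocking studies, the text says: "We do not anticipate this problem with the set up in the outpatient clinic at Changi General Hospital in Singapore". It continues: "If we estimate 10% drop-out, this would mean we would need near to 200 patients to be included in this study".
- **Second paragraph, timetable.** Three patients per week is said to need about 17 months, or 23 months with the 6-month follow-up; 3 years is allowed as a margin. A separate aim is 100 patients in the first 12 months.
- ***Study setting*.** "The trial will take place in Singapore General Hospital, Singapore and Roscommon University Hospital, Ireland". The *Discussion* also speaks of two centres.
- ***Discussion*.** If drop-out is higher than expected, the sample size will be recalculated to "ensure sufficient statistical power regarding recanalisation rates at the end of the trial".

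**The concern.** Two adjacent paragraphs apply the same loss rate and reach targets that differ about twofold. The accrual period and study duration then inherit whichever target was in mind. A reader cannot tell from the text when recruitment is complete, how long the trial should run, or what difference it is powered to detect.

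Three further features make the conflict harder to resolve:

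- The only reason given for expecting 10% loss concerns a clinic that is not among the trial sites.
- The figure of 94, from which any correction would start, does not follow from the inputs printed beside it.
- The *Discussion* speaks of protecting power for recanalisation, but the trial is sized on pain alone and no recanalisation rate or difference is stated.

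**Working it through.** **Inputs (from *Sample size and study duration*).** Difference 20 mm, SD 20 mm, power 90%, alpha 5% (sidedness not stated; two-sided assumed), 94 evaluable in two equal groups, 10% loss, three patients per week, 100 patients in 12 months.

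**1. Reproducing the two targets from 94**

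- Multiplying: 94 × 1.1 = 103.4. This is the printed 103.
- Dividing by the proportion retained: 94 / 0.9 = 104.4, so 105.
- Working back from 200 at 10% loss: 200 × 0.9 = 180 evaluable.
- Loss needed to turn 94 into 200: 1 − 94/200 = 53%. Even the 40% quoted from earlier studies gives only 94 / 0.6 = 156.7, so 157.

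So 103 reproduces and about 200 does not.

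**2. Timetable.** Weeks = N / 3. Calendar months = weeks / (52/12); four-week months = weeks / 4.

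| N | Weeks | Calendar months | Four-week months |
|---|---|---|---|
| 103 | 34.3 | 7.9 | 8.6 |
| 105 | 35.0 | 8.1 | 8.75 |
| 200 | 66.7 | 15.4 | 16.7 |

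Seventeen months at three per week yields 3 × 4 × 17 = 204 patients with four-week months, or 3 × (52/12) × 17 = 221 in calendar months. The stated period therefore goes with the target of 200. For 103 to 105 patients, about 8 months of accrual plus 6 of follow-up is roughly 14 months, not 23.

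The 12-month aim implies 100 / 52 = 1.9 per week, whereas three per week gives 144 to 156 in a year. At 100 per year, 103 patients take 12.4 months and 200 take 24.

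**3. The base of 94.** For two means, n per group = 2 × (z for alpha + z for power)² × (SD / difference)².

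- Two-sided 5%, 90% power: 2 × (1.960 + 1.282)² × (20/20)² = 21.0, rounded up to 22. The t-based calculation gives 23.
- Mann–Whitney adjustment, dividing by a relative efficiency of 0.955 (normal data) or 0.864 (lower bound): 22/0.955 = 23.04, so 24, up to 23/0.864 = 26.6, so 27.
- One-sided 5%: 18 per group.
- Because the phrase describing the 5% level contains the word equivalence, equivalence and non-inferiority with a 20 mm margin were also tried (alpha 5% and 2.5%): 18 to 26 per group.

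None of these gives 47. Conversely, with 47 per group:

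- Power for 20 mm at SD 20 mm is about 99.8%.
- The difference detectable with 90% power is 3.242 × 20 × √(2/47) = 13.4 mm.

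With 180 evaluable (90 per group), that difference is 3.242 × 20 × √(2/90) = 9.7 mm.

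**4. Sites.** *Study setting* lists Singapore General Hospital and Roscommon University Hospital. The drop-out argument names Changi General Hospital, which is not on that list.

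**The case against.** The strongest defence is that nothing here endangers the primary comparison. On the stated difference and SD, either target exceeds 90% power, so this is a drafting contradiction. That is correct about power. It does not tell the reader which number governs recruitment.

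Several stronger readings are tempting, and the document does not support them.

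- **That the timetable fits neither target.** A reader using calendar months might conclude this. With four-week months it gives 204 patients, and in calendar months it is about 10% off, against a figure the protocol calls approximate. It fits 200 and conflicts with 103.
- **That 103 is itself a material error.** Multiplying by 1.1 leaves 103 × 0.9 = 92.7 evaluable, about one patient short of 94. The protocol describes the loss only as of the order of 10%. The method should be corrected, but the effect is trivial.
- **That the right target can be read off as 105, or as equal arms of 53.** This takes 94 as correct, which the stated inputs do not bear out. The *Discussion* also says simple randomisation is used, so equal arms are not guaranteed.
- **That the open range invites stopping on the data.** This is speculation. No interim efficacy analysis is described, the grounds for early stopping are listed separately, and the analyst is to be blinded to allocation.
- **That 10% is refuted by the cited trials.** The *Background* reports 32 dropouts among 111 randomised (29%) in one laser trial and 40 among 109 approached (37%) in another. Those trials followed patients to about 6 weeks and 3 months; the primary outcome here is a 10-day diary. Tracing the protocol's 40% to the 40 of 109 is also a guess. What stands is that the reason offered for 10% concerns an unlisted hospital.
- **That 200 comes from treating 94 as a per-group number.** Doubling gives 188, and 188 / 0.9 = 209. The protocol states 94 as the total, so this remains conjecture.

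Two milder points have some force. The 12-month aim is a milestone and three per week is conditional, so a slow start could explain part of that gap. The recalculation in the *Discussion* is also conditional, though it still presupposes a recanalisation calculation that the protocol article does not give.

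**Conclusion.** The point holds as a contradiction in the recruitment target, together with a base that does not reproduce. From 94 and 10% loss the target is 103 to 105. About 200 would need 53% loss, or 180 evaluable patients whom the protocol article does not justify. The 17- and 23-month figures belong to 200 and are incompatible with 103, by about 9 months of accrual at three per week. The 12-month aim sits poorly with that rate.

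The stated inputs call for about 22 to 23 per group, or 24 to 27 with a Mann–Whitney adjustment, roughly half of the 47 printed. That result assumes a two-sided 5% test, but the one-sided, equivalence and non-inferiority readings tried do not rescue 47 either. The intended size therefore cannot be recovered from the document; only the sponsor can say which inputs were meant.

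The consequence is an undefined enrolment end point and an unreliable timetable, not a loss of power for a 20 mm difference. It should be corrected before recruitment opens.

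**What to change.** 1. **State one target**, with a difference, SD, power, alpha and sidedness that reproduce it. Remove or explain the word equivalence.
2. **Inflate by dividing by one minus the drop-out rate.** If 94 evaluable is kept at 10% loss, the target is 105, and the difference or SD that justifies 94 must be given (for example, about 13.4 mm at SD 20 mm). If about 200 is intended, say what it is for: 180 evaluable gives 90% power for about 9.7 mm at SD 20 mm.
3. **Recompute accrual and total duration** from that target and a single recruitment rate, and make the 12-month aim agree with it.
4. **Justify the drop-out rate at the two listed sites**, or list Changi General Hospital as a site.
5. **In the *Discussion***, tie any recalculation to the number of evaluable 10-day pain diaries, or supply the recanalisation rates and calculation that the power statement presupposes.

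**Cost.** *Trial status* says recruitment has not begun, so the change is protocol wording. If 200 was the operational target, choosing a smaller number reduces precision for the secondary outcomes, including occlusion at 6 months, and that trade-off should be made openly.
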